#### Sample and procedure

The EPEC®-Pediatrics roll-out will include training of five Master Facilitators within Canada; Master Facilitators are individuals qualified to train future EPEC®-Pediatrics Trainers at the face-to-face conference. There are 3 steps to becoming a Master Facilitator: 1) become an EPEC®-Pediatrics Trainer by completing all 19 online modules and attending a face-to-face conference as a participant; 2) attend a Professional Development Workshop offered by EPEC for additional development of teaching skills, and finally 3) teach at an EPEC®-Pediatrics Train-the-Trainer conference where feedback is provided on teaching skills by existing Master Facilitators. At each of the 16 participating sites, 3 to 5 health professionals will be identified as Regional Team members. Each Regional Team member (*n* = 45-80) will become an EPEC®-Pediatrics Trainer through completion of 19 online-modules and 5 face-to-face modules. Two face-to-face sessions will be held over two full days with the content delivered by the new Canadian Master Facilitators in conjunction with the original developers of EPEC®-Pediatrics. Regional Teams will complete the online modules on their own, then attend one of the two-day sessions as a team. At the end of the face-to-face session the new Trainers will be asked to provide feedback on EPEC®-Pediatrics as a whole and assess their learning as part of the process. Feedback will be sought using a Knowledge Transfer and Exchange (KTE) Survey completed in paper based format.

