### Stream 3 - Quality of care

Data collection and analysis in Stream 3 will address the impact of EPEC®-Pediatrics on the quality of palliative care provided to children with cancer and their families. Quality of palliative care will be assessed using data from three sources: A) surveys about symptoms, quality of life, and care quality completed by children receiving active treatment and their parents; B) review of health records of deceased patients; and C) surveys with bereaved parents about the quality of their children’s end-of-life care. Baseline data will be collected through each of the 16 pediatric oncology programs from January to April 2015, to provide a cross-sectional view of the quality of palliative care prior to the EPEC®-Pediatrics roll-out. The same data will be collected again from September to November 2016 to determine the impact of the roll-out on care quality.

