#### Sample size

The majority of quality indicators are categorical in nature (i.e., proportion of children who die in preferred location, proportion of children/parent who report symptoms in the severe range); therefore, sample size for this component of the project was calculated based on categorical analytic techniques. Specifically, sample size for standard Chi-square analysis was conducted and increased by a factor equivalent to the assumed design effect due to the clustering within regions. Given the timeline for the project and the number of children that die from cancer across Canada in a given year (~200), we will only be able to collect data on 100 deceased children in the 6 months following project implementation. However, retrospective health record reviews and surveys can be completed for a larger number of children at baseline. A prior study examining the effect of unit level interventions across 16 pediatric units across Canada, demonstrated moderate intra-class correlations (ICCs) for knowledge outcomes, but negligible ICCs for process and clinical outcomes [35]; therefore, a small ICC of 0.01 was used to adjust the sample size estimate to account for clustering within sites. We will complete a minimum of 200 health record reviews/surveys at baseline and 100 in the post-implementation period across all 16 sites to detect a 15 % difference in outcomes with 80 % power.

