#### Data analysis

Categorical data (e.g., location of care/death) and continuous data (e.g., parent reports of care quality scores) and will be summarized and descriptively reported using frequencies and proportions or means and standard deviations, respectively. To identify differences in the quality indicators between baseline and following implementation, marginal regression models (i.e. Generalized Estimating Equation models) will be used to model the outcome on time point (i.e. pre- versus post-test) and account for clustering of outcomes and practices of care within regions. All analyses will be conducted using SAS v9.3. A *p*-value of 0.05 or less will be used to indicate statistical significance.

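### Stream 3 relies on GEE at p ≤ 0.05 with only 16 site clusters; with the customary uncorrected robust variance the two-sided error would be about 7–9%, so a small-sample correction should be stated

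*Protocol article*

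**What the plan says.** The Data analysis section under Stream 3 of the protocol article gives one inferential method for the quality indicators. It plans marginal regression, described as "Generalized Estimating Equation models) will be used to model the outcome on time point" (pre versus post), fitted so as to "account for clustering of outcomes and practices of care within regions". A p-"value of 0.05 or less will be used to indicate statistical significance", and "All analyses will be conducted using SAS v9.3".

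The number of clusters follows from the design. Stream 1 states that "At each of the 16 participating sites, 3 to 5 health professionals will be identified as Regional Team members", so each site has one Regional Team and the natural reading of region is site. The Stream 3 introduction says "Baseline data will be collected through each of the 16 pediatric oncology programs from January to April 2015". The Sample size section sets a "minimum of 200 health record reviews/surveys at baseline and 100 in the post-implementation period across all 16 sites", with an ICC of 0.01, to "detect a 15 % difference in outcomes with 80 % power".

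The article names no variance estimator (robust or model-based), no reference distribution (z or t), no working correlation and no SAS procedure.

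**The concern.** GEE inference is usually based on the robust (sandwich) variance, because that variance stays valid if the working correlation is wrong. Its justification is asymptotic in the number of clusters, not the number of children. With 16 clusters the fitted residuals are too small on average, so the uncorrected sandwich variance is biased downward. It is also itself variable, which a normal reference ignores. Both effects make p-values too small, and the bias grows when a few large sites dominate.

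The stakes are real. There is no control group, and this model is the only stated formal test of whether care quality changed. The Sample size section refers to many quality indicators, so any inflation would apply to each of several tests.

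**Working it through.** **1. The plan's own figure.** The stated figure is 80% power for a 15% difference. The baseline proportion is not given, so it cannot be reproduced uniquely. Assumptions: 15 percentage points, two-sided 0.05, pooled two-proportion test, sample sizes divided by the design effect 1 + (m − 1) × 0.01.

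- m = 300/16 = 18.75 gives 1.1775; m = 200/16 = 12.5 gives 1.115.
- Power = Φ[(0.15 − 1.96 × SE₀)/SE₁], where SE₀ uses the pooled proportion and SE₁ the separate ones.
- 15% vs 30%, design effect 1.1775: effective n = 169.9 and 84.9, SE₀ = 0.0532, SE₁ = 0.0568, power 0.790. With 1.115 it is 0.811.
- 50% vs 65%: power 0.624 and 0.648.

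So 80% is reachable at a low baseline proportion. The calculation takes a true 5% level as given; it says nothing on whether the GEE test delivers that level.

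**2. Inputs for the error rate.** From the article: 16 sites, 200 pre and 100 post (200/16 = 12.5 and 100/16 = 6.25 per site), ICC 0.01, level 0.05. Assumed and varied: event rate 0.2 or 0.5; ICC 0, 0.01 or 0.05; correlation of pre and post site effects 0.5 to 1; coefficient of variation (CV) of site size 0, 0.6 or 1.0; exchangeable or independence working correlation. Two-sided testing is also assumed, since the article does not state sidedness.

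**3. Estimators.** The uncorrected sandwich is B⁻¹(Σᵢ Dᵢ′Vᵢ⁻¹rᵢrᵢ′Vᵢ⁻¹Dᵢ)B⁻¹, with B = Σᵢ Dᵢ′Vᵢ⁻¹Dᵢ. Mancl-DeRouen replaces the residual vector rᵢ by (I − Hᵢ)⁻¹rᵢ, and Kauermann-Carroll by (I − Hᵢ)^(−1/2)rᵢ, where Hᵢ is the cluster leverage. Degrees of freedom are 16 − 2 = 14 (intercept and time point) or 16 − 1 = 15.

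**4. Results under no pre/post change.** There were 6,000 runs per scenario; the Monte Carlo standard error near 8% is √(0.08 × 0.92/6000) = 0.35 points.

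| Inference at nominal 0.05 | Rejection, range over scenarios |
|---|---|
| Uncorrected sandwich, z, equal sites | 7.4–8.7% |
| Uncorrected sandwich, z, CV 0.6 | 7.2–9.1% |
| Uncorrected sandwich, z, CV 1.0 | 9.3–10.8% |
| Uncorrected sandwich, z, improvement only (nominal 2.5%) | 3.6–5.6% |
| Uncorrected sandwich, t(14) | 5.0–8.2% |
| Kauermann-Carroll type, t(14) | 4.2–6.7% |
| Mancl-DeRouen, t(14) | 3.5–5.4% |
| Model-based, z | 3.9–6.9% |

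**5. Cross-check.** A separate simulation (independence GEE, event rate 50%, ICC 0.01, 8,000 runs) gave, for sandwich z, sandwich t(15), Mancl-DeRouen z and Mancl-DeRouen t(15): 7.4, 5.4, 5.6 and 3.8% with equal sites, and 9.0, 6.8, 6.4 and 4.6% with site shares of 1–16%. A further run gave 7.5–7.7% (equal) and 8.4–9.2% (uneven) for sandwich z, against 4.0–4.8% for Mancl-DeRouen with t(15). The three sets agree.

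**The case against.** The strongest objection is that the article never says the standard errors will be uncorrected. Naming SAS v9.3 does not settle it, because corrected estimators are available in SAS. A t reference alone removes much of the excess (5.0–8.2%), and model-based errors stay at 3.9–6.9% in the settings tried. A journal article commonly leaves the variance estimator and degrees of freedom to the full protocol or analysis plan, so the silence is not itself a fault.

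All of that stands, and it rules out some stronger readings. A reader might infer that the plan as written has a true error rate of 7–10%. The article does not support this, because it does not choose the estimator that produces that rate. A reader might also attach 7–10% to false improvements; that range is two-sided and includes false deteriorations, so improvements alone are about half of it. Nor can one say that the reported confidence intervals will be too narrow, since the Data analysis section mentions none.

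What the objection does not remove is that GEE at 0.05 with 16 clusters is what the article does commit to. In its most customary form, that method misses the stated level in every scenario examined. Model-based errors would largely avoid this, but they depend on a correct working correlation, and the article does not choose them either.

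**Conclusion.** The point holds as a conditional one, and the change is a worthwhile, inexpensive improvement. If Stream 3 uses the uncorrected robust variance with a z reference, the two-sided error is about 7–9% in place of 5%, rising to about 11% when site sizes are very uneven. False improvements alone would be about 4–5% against 2.5%.

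The result rests on 16 clusters, the minimum totals of 200 and 100, two-sided testing, and assumed event rates and site sizes. The lower part of the range needs no unevenness: equal sites at the protocol's ICC of 0.01 already give 7.4–8.7%. If regions are units larger than the 16 sites, there are fewer clusters and the inflation would probably be greater; that was not simulated. Confidence is high in the simulated rates, and lower in whether this trial would use that estimator.

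**What to change.** Add one sentence to the Stream 3 analysis: GEE inference will use a small-sample-corrected robust variance (Mancl-DeRouen or Kauermann-Carroll, for example through the EMPIRICAL options of PROC GLIMMIX) with a t reference on 14 or 15 degrees of freedom, taking the 16 sites as clusters. Mancl-DeRouen is the safer of the two if sites are very uneven, since its rejection rate did not exceed 5.4% in any scenario.

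The cost is a different procedure option and somewhat less precision. The t reference alone widens intervals by 2.145/1.960 = 1.09 (14 df) or 2.131/1.960 = 1.09 (15 df), before the correction to the standard error. Putting 2.145 in place of 1.96 in the power formula above (design effect 1.1775) moves 15% vs 30% from 0.790 to 0.737, and 50% vs 65% from 0.624 to 0.551. That is roughly 5 to 7 points by this approximation, part of the price of a test that holds its level.

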#### Sample and procedure: A) Surveys during active treatment

Parents of children with a cancer diagnosis who are receiving treatment through one of the 16 pediatric oncology programs in Canada will be invited, along with their child, to complete a survey about symptoms, quality of life, and care quality. Parents will be eligible to take part if the child is less than 19 years of age, has a cancer diagnosis, and they are able to understand and read English or French. Parents will be excluded if the child is disease-free and has not received cancer-directed therapy in the last 3 months or if the health professional involved in their care feels the family should not be approached for research participation at this time (e.g., a recent relapse, difficulty coping with child’s illness, etc.). Children aged seven years or older who meet the same criteria as the parents will be invited to complete their own survey about symptoms and quality of life.

The Parent Survey has been adapted from ‘The Survey About Caring for Children With Cancer’ (SCCC) [9, 31, 32] and the ‘Quality of Children’s End-of-Life Care Instrument’ (QCECI) [33]. The SCCC, developed by one of our co-investigators (JW), is a widely used comprehensive, self-administered survey that evaluates parents’ perceptions of the child’s illness and care quality. It was originally developed from a literature review and focus groups with parents and health professionals to identify key domains, and underwent pretesting to assess content, wording, response burden, and cognitive validity [9, 31, 32]. The QCECI was developed in a similar manner as the SCCC and tested for reliability and validity by one of the co-PIs (KW), with bereaved mothers [33]. It has also been adapted and used with parents prior to the child’s death to assess care quality. The Parent Survey will take approximately 15-30 min to complete.

The Child Survey consists of the ‘Memorial Symptom Assessment Scale’ [25, 26] and the ‘Pediatric Quality of Life Inventory’ (PedsQL™) 4.0 generic module [34] to assess symptoms and quality of life as well as questions asking how often they are asked about symptoms and quality of life by health professionals. The Child Survey will take approximately 15-20 min to complete.

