#### Sample and procedure: B) Health record reviews

Health record reviews will be conducted for all children with a cancer diagnosis who received treatment at one of the 16 pediatric oncology programs and died in the 12 months prior to the pre-test data collection (January 2014 to January 2015) and in the 6 months prior to the post-test data collection (June to November 2016).

Eligible deceased children will be identified through the Health Records Department. An on-site RA will review the health record and enter data directly into REDCap™. Data collection forms were developed based on previous health record reviews for children with cancer [9, 31, 32] and include information on diagnosis, age, location of death, involvement of a palliative care team, time spent in hospital during the last month of life, use of cancer directed treatments, and documentation of discussion of goals of care.

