The Bereaved Parent Survey was adapted from the SCCC [9, 31, 32] and QCECI [33] to mirror the survey used during active treatment, with additional items specific to the quality of end-of-life and bereavement care. Contact information (name and mailing address) of eligible parents will be obtained through Health Records. A letter about the study will be sent to eligible parents from someone who provided care to the family prior to the child’s death or who is providing bereavement follow-up. The letter will include a description of the study with instructions to access the survey online for submission via REDCap™. The letter will also provide contact information for a RA at the central study site if the parent wishes to complete the survey with the RA by telephone or to request a hard copy to complete and return by mail. When the parent accesses the survey online, the consent form will appear prior to commencing the survey questions along with a list of sources of support and information. Submission of the survey will signify consent. The invitation letter will also include a self-addressed stamped envelope to be returned to the originating site if the parent does not wish to have any further contact about the study (opt-out). If an opt-out letter has not been received, a thank you/reminder letter will be sent to all eligible parents 3-4 weeks after the initial contact.

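### Stream 3 judges an unstated number of quality indicators from three sources at p ≤ 0.05 each, with no primary indicator or multiplicity control, and its 80% power belongs to none of them

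*Protocol article*

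**What the plan says.** The Stream 3 introduction states that "Quality of palliative care will be assessed using data from three sources": surveys of families during active treatment, health record reviews of deceased children, and surveys of bereaved parents.

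The content that could become an indicator is described source by source:

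- The active-treatment survey asks families "to complete a survey about symptoms, quality of life, and care quality". Children also report symptoms, quality of life and how often staff ask about these.
- The record review collects, among other items, "location of death, involvement of a palliative care team, time spent in hospital during the last month of life, use of cancer directed treatments", and whether goals of care were documented as discussed.
- The bereaved-parent survey mirrors the active-treatment survey, "with additional items specific to the quality of end-of-life and bereavement care".

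The Sample size section says "The majority of quality indicators are categorical in nature" and gives two examples. It then plans at least 200 records or surveys at baseline and 100 afterwards, for a 15% difference with 80% power and an intra-class correlation of 0.01. No base rate and no specific indicator is attached to that figure.

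The Stream 3 Data analysis section sets the purpose, "To identify differences in the quality indicators between baseline and following implementation". It says that marginal regression models "will be used to model the outcome on time point (i.e. pre- versus post-test", and it closes with the single threshold of a p-value "of 0.05 or less will be used to indicate statistical significance". The Discussion adds that the study has the power to pick up changes in care quality.

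**The concern.** Research question 4 asks whether the programme affects the quality of palliative care. The article does not say which indicator answers it. Streams 1 and 2 do have explicit targets: 5 Master Facilitators, 45 Trainers and 600 End-Users, and 10 of 16 teams reaching their improvement goals. Stream 3 is the only stream with a power calculation and significance tests, and it has no such criterion.

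With many indicators each held to 0.05 and none ranked above the others, the chance that at least one crosses the line without any true change is well above 5%. The design is an uncontrolled pre-post comparison, so there is no comparison group against which to check an isolated significant result. The power claim is affected too: power for a 15-point difference depends on the base rate, and no base rate can be assigned until an indicator is named.

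**Working it through.** **1. The plan's own figure.** Inputs from the Sample size section: 200 at baseline, 100 after, a 15% difference (read here as percentage points), 80% power, intra-class correlation 0.01, 16 sites. Assumptions: two-sided 0.05, pooled chi-square without continuity correction, design effect 1 + (m − 1) × 0.01.

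- With m = 100/16 = 6.25, the design effect is 1 + 5.25 × 0.01 = 1.0525. For 30% versus 15% (or 70% versus 85%), 196 and 98 are needed and power at 200/100 is 81%. This is close to the stated figure.
- For 50% versus 65%, power at 200/100 is 70% with no inflation. It is 67% with design effect 1.0525 and 62% with 1.1775 (m = 300/16).

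The stated 80% can therefore be neither confirmed nor refuted. It holds for some base rates and not for others.

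**2. Number of tests.** The documents do not give k, the number of indicators, so a range is used. Counting the named content domains once each gives about 14: five from the record review; three from parents in active treatment; three from children; and end-of-life care, bereavement care and death in the preferred place for bereaved parents. That is a count made for this check, not a figure in the article.

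**3. Error rates with no true change.** Sidedness is not stated. Two-sided tests are assumed because the aim is worded as finding differences. For k independent tests:

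- at least one false significant difference, either direction: 1 − 0.95^k
- at least one false significant improvement: 1 − 0.975^k

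For correlated indicators, equally correlated normal test statistics were used, with the same correlation ρ for every pair.

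| k | Either direction, independent | Improvement, independent | Improvement, ρ = 0.3 | Improvement, ρ = 0.5 | Improvement, ρ = 0.7 |
|---|---|---|---|---|---|
| 1 | 5.0% | 2.5% | – | – | – |
| 5 | 22.6% | 11.9% | 10.5% | 9.1% | 7.4% |
| 10 | 40.1% | 22.4% | 17.8% | 14.4% | 10.7% |
| 14 | 51.2% | 29.8% | 22.4% | 17.4% | 12.4% |
| 20 | 64.2% | 39.7% | 28.0% | 21.0% | 14.5% |

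At k = 14, the either-direction figure falls to 43.8%, 34.8% and 24.9% for ρ = 0.3, 0.5 and 0.7. Even at ρ = 0.7 the chance of a false improvement is about five times that of one named test (12.4 / 2.5 ≈ 5).

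**The case against.** The strongest reply is that this is a condensed article. Indicator lists, rankings and adjustment methods are commonly left to an analysis plan, which is not shown. That stands for the detail. It does not cover the deciding outcome, which is a core design element. The article itself fixes the significance threshold, a power statement and the claim that the study can detect changes in care quality, and it attaches none of these to an indicator. The only analysis it presents as exploratory is a different one, on how roll-out differences between sites relate to care quality.

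Three stronger readings are tempting, and the documents do not support them:

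- *A false improvement is about as likely as not.* The 51% at k = 14 counts false results in both directions and assumes independence. Under two-sided testing, a false improvement reaches 50% only near k = 28 (1 − 0.975^28 = 50.8%). Fourteen tests would suffice only if each were one-sided at 0.05, which the article does not say. Indicators reported by the same respondents, or read from the same charts, are also likely to be correlated.
- *The article specifies 14 indicators.* It lists form contents and survey domains, and gives only two examples of quality indicators.
- *One significant indicator is declared sufficient to show impact, so the result cannot be interpreted.* The threshold defines when a comparison is called significant. Nowhere does the article say that a single one establishes impact. Each pre-post difference can still be read on its own terms. What is missing is a rule for drawing the overall conclusion.

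**Conclusion.** The point holds in this form: Stream 3 tests an unranked set of indicators from three sources at an unadjusted 0.05, with no indicator named to answer research question 4 and a power statement that belongs to none of them. The inflation is material but cannot be pinned to one number. For 5 to 20 independent two-sided tests with no true change, it is 23% to 64% for any false significant difference and 12% to 40% for a false improvement, against 5% and 2.5% for one named test. Positive correlation reduces it; at 14 indicators with correlation 0.3 to 0.7, a false improvement has a chance of 22% to 12%. These figures rest on an assumed number of indicators, an assumed correlation and two-sided testing, none of which the article states.

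**What to change.** Before post-test data are seen, name one primary care-quality indicator and test it at 0.05. The choice is the sponsor's. An item from the record review is preferable, because that review covers all deaths in its windows and has no survey non-response. In choosing, note that some record items are the direct target of only one optional improvement kit; documented goals-of-care discussion is an example. Attach the 80% power statement to the chosen indicator, with its assumed base rate.

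Report all other indicators as secondary, as estimates with 95% confidence intervals and no significance claims. If significance claims are wanted, apply one adjustment, such as Holm, across all secondary indicators together. Adjusting separately within each source would leave three families at 0.05 each, or 1 − 0.95^3 = 14% if independent. Benjamini-Hochberg controls a different error rate from the one at issue here.

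The cost is wording, with no new data. Fewer indicators could be called significant. If the chosen indicator has a base rate near 50%, the power statement would need restating, since 200 and 100 then give 62% to 70% under the assumptions above.
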